### 2.7. Sample Size Calculation

Considering the attrition rate, we will recruit 260 students to obtain 200 study completers. A total of two-hundred participants will allow to detect an effect size of at least d = 0.40, fixing a power (1 − β) of 80%, and an alpha of 0.05 (two-tailed) in a between group comparison (e.g., comparing the two treatments). This sample size is similar to Harrer et al. [25]. The effect size is estimated considering a recent meta-analytic review for Internet-based stress interventions which reports effect sizes ranging between d = 0.32 and d = 0.64 [81].

Frequentist and Bayesian approaches have their own advantages and drawbacks in data analysis. We will adopt both to provide robust evidence to the specific statistical approach.

We conducted a Bayes Factor Design Analysis (BFDA) [82] (i.e., the counterpart of power analysis in the Bayesian world) to estimate the Bayesian analysis sensitivity, given the sample size of 200 people. We simulated 10,000 results, fixing the Bayes Factor (BF) decision boundary at 10, and an estimated effect size for a true H1 equal to d = 0.40. The BFDA simulation was performed for a default prior (i.e., a Cauchy distribution with a scale = 0.707) and an informative prior (i.e., a t distribution with μ = 0.35, df = 3, r = 0.102), considering true H0 (i.e., d = 0) and H1 (d = 0.40). Given those parameters, we estimate to surpass the decision boundary for H1 in 87.8% adopting the default prior and 93.8% of the case adopting the informed prior. In the case of a true H0, the decision boundary is surpassed in 45.5% and 62.2% of the cases adopting the default or the informed prior, respectively. The design is robust to the misleading evidence, showing a false positive evidence rate of 0.002 and 0.006 adopting the default or the informed prior. No false negative evidence has been observed over 10,000 simulations with any of the two priors. In the case of inconclusive evidence, we will increase the sample size until the BF decision boundary is surpassed (BF > 10) in either one of the two directions supporting H1 or H0.

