For what concerns the predictive model, we will explore the possibility to use ML algorithms to tune a model able to predict the responders on each of the primary outcomes starting from the socio-demographic information collected and the primary and secondary outcome measures in two steps. First, we will use only socio-demographic information to predict the primary outcome measure of each module. Second, we will use the socio-demographic information, the other primary, and all the secondary outcome measures to predict the primary outcome of each specific module. Before entering an outcome measure as a target variable (i.e., to be classified/predicted variable), variables have to be dichotomized. We will classify participants as responders or non-responders, adopting the minimum clinical importance difference and adopting a distribution approach [85]. A responder will be defined as a participant that records a change larger than 1 standard error of the mean (SEM) calculated on the baseline distribution. For example, the effectiveness of the first module is measured primarily on the BDI-II scale. We will first identify participants that change more than 1 SEM to classify responders and non-responders. Then we will use ML algorithms to predict this outcome starting from socio-demographic in a first step, and socio demographic plus the other outcome variables (except BDI-II of course) in a second step. We will test five different algorithms to have a good mixture of simple linear (LDA), nonlinear (CART, kNN), and complex nonlinear (SVM, RF) methods, thus covering the most used and diffused ML methods [86]. A total of 20% of the data will be held out for testing purposes, thus ML training will be performed on the remaining 80% data of the total sample. The portion of sample holdout will be set at the beginning and kept constant for all the algorithms tested and outcomes targeted, to make the different models’ performances directly comparable.

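### One fixed 20% hold-out of about 40 people gives an unbiased but very imprecise accuracy and ranks the five algorithms only weakly

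*Protocol article*

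**What the plan says.** The Protocol article, 2.8. Statistical Methods, describes machine-learning models that are to "predict the responders on each of the primary outcomes", in two predictor steps: socio-demographic data alone, then with the other outcome measures added. Five algorithms are compared: LDA, CART, kNN, SVM and RF.

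The evaluation design is one split: "A total of 20% of the data will be held out for testing purposes", while "ML training will be performed on the remaining 80% data of the total sample". The held-out people are fixed at the start and "kept constant for all the algorithms tested and outcomes targeted". The stated reason is "to make the different models’ performances directly comparable".

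The number of people comes from 2.7. Sample Size Calculation: "we will recruit 260 students to obtain 200 study completers". The article gives neither a count for the hold-out nor a target precision for model accuracy. The Aims and Hypotheses section describes this work as exploratory.

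**The concern.** The hold-out has two jobs: to say how accurate each model is, and to let five models be compared. Both depend on how many people are in it, and 20% of the planned completers is few. Every score also comes from the same draw, so an unlucky split would affect all algorithms and outcomes together, and agreement across outcomes would not be independent confirmation.

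At stake is the fourth hypothesis, that the data will allow predictors of treatment response to be identified. With a test set this small, a useful model and a nearly useless one can score alike, and the order of the algorithms may owe much to which people were held out. This is a stated choice with a stated reason, so it can be assessed on the article alone.

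**Working it through.** **Inputs from the article.** 260 recruited, 200 completers, d = 0.40, 80% power, two-sided alpha 0.05 (2.7); 1:1 allocation (2.3); 20% hold-out, 80% training, five algorithms, one constant split (2.8).

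**Assumptions.** The article gives no true accuracy, no correlation between the algorithms' errors and no discordance rate. I take accuracy near 70%, error correlation 0, 0.5 and 0.8 on a latent normal scale, and discordance of 20% and 30%.

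**1. The plan's own figure.** n per arm = 2 × (1.96 + 0.842)² / 0.40² = 98.1, so 99 per arm and 198 in total, in line with 200. Power at 100 per arm is 80.4% (noncentral t). Implied attrition is 60/260 = 23.1%, and 200 / (1 − 0.231) = 260. The planned numbers reproduce.

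**2. Size of the hold-out.** 0.20 × 200 = 40 tested and 160 for training. If all 260 have data, 0.20 × 260 = 52.

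**3. Precision of one accuracy.** Half-width = 1.96 × √(p(1 − p)/n).
- n = 40, p = 0.70: 1.96 × √(0.21/40) = 0.142, or ±14 points. The exact (Clopper-Pearson) interval for 28/40 is 53% to 83%.
- 24/40 (60%): exact interval 43% to 75%, which includes 50%.
- n = 52: 36/52 (69%) has an exact interval of 55% to 81%.
- For ±10 points at 70%: n = 1.96² × 0.21 / 0.10² = 80.7, so 81 test cases. At a 20% share that is 81/0.20 = 405 completers.

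**4. Ranking five models on 40 shared people (simulated).**

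| True accuracies | Best model comes first |
|---|---|
| 70% v 65% for the other four | 38–50% |
| 75% v 65% for the other four | 61–80% |

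Chance alone would give 20%. Exact McNemar power for a 10-point paired difference is 18% at 20% discordance and 13% at 30%.

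**5. Optimism if the winner is chosen and scored on the hold-out (simulated).**

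| Error correlation | Five equal models at 70% | One model 10 points better |
|---|---|---|
| 0 | 8.2 points | 6.2 points |
| 0.5 | 6.8 points | 4.4 points |
| 0.8 | 5.3 points | 2.4 points |

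If the algorithm is instead chosen on the training data only, the simulated optimism is about 0.

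**6. All 200 tested out of fold.** Half-width = 1.96 × √(0.21/200) = 0.064, or about ±6 points. McNemar power for a 10-point difference rises to 69–87%. Both figures treat the 200 predictions as independent, ignoring dependence between folds, so they are approximate. Picking the winner on those 200 scores would still overstate accuracy by 2.4 to 3.8 points for five equal models at 70%, so any choice of a best model belongs in the inner folds.

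**The case against.** The strongest case for the plan has six parts.

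- **A common test set is good design.** Scoring all algorithms on the same people gives paired comparisons. This stands, and the remedy keeps it.
- **A reader might infer that the hold-out cannot measure or rank at all.** The article does not support that. A model fixed in advance gets an unbiased estimate, and one that is truly 10 points better comes first in 61–80% of trials. The ranking is weak, not absent.
- **A reader might infer that the plan will report an inflated accuracy for its best model.** The article never says that a winner will be chosen on the hold-out and its score there reported. Reporting all five fits the text equally well. Choosing a model by cross-validation inside the 80% is also compatible with it, and such detail may sit in a fuller plan. The optimism is therefore conditional.
- **A reader might infer that reuse across outcomes is itself a bias.** It is not. It makes the results depend on the same draw without shifting any single outcome's accuracy.
- **Forty is not certain.** It could be 52, and 2.7 lets the sample grow if the Bayesian evidence is inconclusive. At 52 the interval is only slightly narrower.
- **A hold-out set aside at the start guards against leakage, and the aim is exploratory.** Both are true. But an untouched set of 40 validates little, and exploratory status does not make the estimates more precise.

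What remains is the imprecision and the weak ranking. Both follow from the stated split.

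**Conclusion.** The point holds as a cheap improvement to an exploratory analysis. The single split leaves an accuracy near 70% known only to about ±14 points, and gives about 13–18% power to show a 10-point difference between two algorithms. The plan is right that a common split puts the models on the same footing, but about 40 people are too few to separate realistic differences.

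The hold-out count follows from the article's own 20% and 200 completers, and the interval needs only that count and an accuracy near 70%. The ranking, power and optimism figures also rest on the assumed error correlations and discordance, and are therefore given as ranges. The optimism, about 5–8 points for equal algorithms and about 2–6 when one is truly 10 points better, applies only if selection and scoring both use the hold-out.

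Nothing here touches the randomised efficacy comparison.

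**What to change.** In 2.8. Statistical Methods, replace the single split by repeated nested cross-validation on the whole analysed sample, for example five outer folds, repeated. Use the same folds for all algorithms, which keeps the pairing the plan wants. Confine tuning, and any choice of a best model, to the inner folds. Report out-of-fold accuracy with intervals, and paired differences between algorithms. With five outer folds each model still trains on about 160 people, as now, while all 200 serve as test cases.

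The cost is computing time and a sentence or so of wording; no further participants or data are needed. The downside is that no untouched test set remains, so external validation is left to later data.

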### Aims and Hypotheses

MindBlooming is a two-year research project with multiple primary goals and related hypotheses. Firstly, we aim to design and implement a new Internet-Based Multi-Approach Intervention (IB-MAI) for university students. The intervention covers a wide range of mental health issues that are relevant within the university student population [11,28] and that are treatable with IBIs [23,25,29]. Furthermore, the intervention is tailored to the individual’s needs. The mental health issues that MindBlooming addresses are depression, anxiety, sleep problems, self-disruptive thoughts, job- and study-related stress and burnout, and chronic pain.

Secondary aims will be: (1) the feasibility assessment of this IB-MAI (in terms of acceptability, satisfaction, usability, and uptake) through a pilot study on a restricted sample; (2) a randomized controlled trial (RCT) to compare the IB-MAI with web-education, as the control condition (CC); and (3) exploratory analysis to tune a predictive model on the collected data adopting Machine Learning techniques.

We hypothesize that: (1) the design and implementation of the IB-MAI treatment will be feasible; (2) the majority of the students will accept and be satisfied with the treatment; (3) the IB-MAI will be superior to the CC on both the primary and secondary outcome measures; and (4) the large amount of collected data will allow the identification of predictors of treatment response and different trajectories in treatment response.

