### 2.4. Intervention

MindBlooming is conceived as an Internet-Based Multi-Approach Intervention (IB-MAI) intended to provide psychoeducation and teach new strategies to cope with different psychological problems. We consider MindBlooming to be multi-approach since it integrates different psychotherapeutic strategies such as Cognitive Behavioral Therapy [35], Acceptance and Commitment Therapy [36], Mindfulness-Based Cognitive Therapy (MBCT) [37,38], Mindfulness-Based Stress Reduction (MBSR) [39], and Dialectical Behavioral Therapy [40]. All these interventions are evidence-based and several studies proved their efficacy in treating different psychological conditions (for an overview, see [41] and APA division 12 list of research-supported psychological treatments, https://div12.org/psychological-treatments/, accessed date 29 December 2021). The intervention consists of 6 interactive modules: depression, anxiety, sleep problems, self-disruptive thoughts, job- and study-related stress and burnout, and chronic pain. A total of two modules will be assigned to each participant based on the initial screening and specific requests and preferences. In addition to the assigned treatments based on the initial screening, all participants will receive a separate training to improve their relational and empathy skills: during the 6th week, they will have access to two videos focused on the importance of relationships on our health, social support as a protective factor, social isolation and loneliness as a risk factor, emotion regulation, and empathy. Afterward, they will have access to a set of exercises, including quizzes about social relationships, assertive communication training, DBT [40], and Interpersonal Psychotherapy (IPT) for Depression strategies (which correlate depressive symptomatology to relational problems) [42]. Moreover, during the 7th week of treatment, more contents in the same formats (videos, texts, and quizzes) will be proposed, focusing on emotions and relationships problems related to the specific issues faced in the assigned modules (e.g., problems in relationships in association with depressive symptoms).

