### 2.6. Outcome Measures

Participants will be screened with a complete online battery to assess their symptoms, including both primary and secondary outcome measures, at pretreatment baseline (T0), after the 7-week IB-MAI treatment, or CC completion (T1), at 12-week follow-up (T2), and 24-week follow-up (T3) (see Figures S1 and S2 for the study design and assessments). Moreover, at pretreatment time (T0), socio-demographic questions are included; these concern marital status, educational qualification, employment status, physical or psychiatric illnesses, and past or current therapies. Questions related to gender and the COVID-19 pandemic are included to investigate the influence of the pandemic on students’ mental health status. These items were drawn up according to the International COVID-19 Suicide Prevention Research Collaboration guidelines [56]. In contrast, those relating to gender were taken from the Williams Institute of the UCLA School of Law for health surveys [57].

Since participants have a timeframe to begin and complete each week of treatment, the overall treatment duration can differ among subjects. Therefore, post-treatment and follow-up time points will be calculated for each participant, starting from the end of the last activity.

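### As written, the predictive models pool both arms without randomised arm as a predictor, so they dilute predictors of response to IB-MAI and cannot tell them from prognostic factors

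*Protocol article*

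**What the plan says.** The question is set in Aims and Hypotheses, where hypothesis 4 expects that "the large amount of collected data will allow the identification of predictors of treatment response and different trajectories in treatment response". Section 2.7 repeats the aim of finding treatment response predictors.

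Section 2.8 then fixes the method:

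- **Training data.** "ML training will be performed on the remaining 80% data of the total sample". One hold-out serves every model: "The portion of sample holdout will be set at the beginning and kept constant for all the algorithms tested and outcomes targeted".
- **Predictors, step 1.** "First, we will use only socio-demographic information to predict the primary outcome measure of each module".
- **Predictors, step 2.** "we will use the socio-demographic information, the other primary, and all the secondary outcome measures to predict the primary outcome of each specific module".
- **Target.** A participant is a responder if the change exceeds 1 standard error of the mean of the baseline distribution. This is a within-person change.

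Section 2.6 describes the socio-demographic items: "these concern marital status, educational qualification, employment status, physical or psychiatric illnesses, and past or current therapies", plus questions on gender and COVID-19. Neither allocation nor module is among them.

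Section 2.3 randomises 1:1 to IB-MAI or the control condition (CC), which receives websites. In IB-MAI, "A total of two modules will be assigned to each participant based on the initial screening" (section 2.4), and everyone also receives relational training.

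**The concern.** Response to a treatment is a contrast: what happens with it against what would have happened without it. The trial is randomised and so holds the information needed for that contrast, but the stated models do not use it. A control participant who improves gets the same label as an IB-MAI participant who improves, and no listed predictor lets the model tell them apart.

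If the results are reported under hypothesis 4, factors that merely mark a good natural course could be presented as markers of who benefits from the app. Features that truly modify the app's effect would appear weaker than they are. Anyone using the results to decide which students to offer the app would be relying on prognosis.

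**Working it through.** **1. The plan's own figure.** The only sample-size figure is for the between-group comparison: d = 0.40, 80% power, two-sided alpha 0.05 (section 2.7).

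- n per arm = 2 × (1.960 + 0.842)² / 0.40² = 98.1, rounded up to 99, or 198 in total. The exact t-test gives 99.1 per arm, and power at 100 per arm is 80.4%. The stated 200 completers reproduce.
- 260 recruited to 200 completers implies attrition of 1 − 200/260 = 23.1%.
- The predictive models have no figure of their own. The 80/20 split of 200 gives 160 for training and 40 for testing. About 80 of the 160 would be IB-MAI if attrition is equal between arms.

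**2. What the pooled model estimates.** Let D1 and D0 be the difference in responder percentage between two levels of a feature within IB-MAI and within CC. Randomisation makes a baseline feature independent of arm, so with equal arms:

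pooled contrast = (D1 + D0) / 2

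The treatment-response question asks about D1 − D0, which the average does not determine. A pooled contrast of 10 points fits each of these:

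- D1 = 20, D0 = 0: pure treatment modifier, difference 20
- D1 = 10, D0 = 10: pure prognostic factor, difference 0
- D1 = 0, D0 = 20: a factor that matters only without the app, difference −20

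I assume here that the outcome measures used as predictors in step 2 are baseline values. No baseline variable can stand in for a randomised arm.

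**3. Share of responders who are controls (illustrative).** Assumptions, not trial figures: control improves 0.2 SD, IB-MAI 0.6 SD, T0–T1 correlation 0.6. The SD of change is √(2 × (1 − 0.6)) = 0.894. The written threshold, 1 standard error of the mean at n = 200, is 1/√200 = 0.07 SD.

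- CC responders: Φ((0.2 − 0.07)/0.894) = 56%
- IB-MAI responders: Φ((0.6 − 0.07)/0.894) = 72%
- Control share of all responders: 56 / (56 + 72) = 44%

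With a stricter cut of 0.5 SD, which is not the protocol's rule, the figures are 37%, 54% and about 40%.

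**4. Logistic simulation (400,000 subjects, 1:1, assumed effects).** Pooled without arm, against a model with arm and arm-by-feature terms:

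- Purely prognostic feature: pooled coefficient 0.73; arm interaction 0.01.
- Feature acting only under treatment: pooled 0.34; arm interaction 0.85.
- Feature with opposite effects in the two arms: pooled −0.04; arm interaction 1.34.
- No treatment effect at all (47.5% responders in each arm): the pooled model still returns the prognostic feature with coefficient 0.82.

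The last case shows the problem most plainly: the pooled model finds a strong predictor of response to a treatment that does nothing.

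**5. Size of single-module subsets.** If the six modules are used equally, 2/6 × 200 = 67 completers across both arms share a given problem area. That is 53 for training and 13 for testing, or about 27 and 7 per arm.

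**The case against.** **Pooling is inferred.** The sentence on the 80% share sets a split and does not explicitly define a population, and the wording about specific modules might suggest a restriction. That is a fair caution. But nothing narrows the sample, the article describes only a two-arm trial sample for this analysis, and one constant hold-out for all outcomes fits the whole-trial reading. If only IB-MAI were used, the models would predict improvement under treatment and still could not separate prognosis from response.

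**This is detail left to a fuller plan, in an exploratory analysis.** The exploratory label limits the consequence, and the efficacy comparison in section 2.8 is separate and unaffected. But the article states the training data, both predictor sets and the target, and together these do not answer hypothesis 4. The point concerns a stated specification rather than a missing one.

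**The harm can be overstated.** This stands, in three respects:

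- A reader might infer that the models cannot pick up treatment modifiers at all. They can: a modifier acting only under treatment is diluted to about half, and only opposite effects in the two arms cancel.
- A reader might infer that prognostic factors will necessarily outrank modifiers. That depends on effect sizes which the document does not give.
- A reader might infer that only one sixth of the sample (1/2 × 2/6, about 33 of 200) received the treatment being modelled. That needs equal module use. If 60% took the depression module it would be 1/2 × 0.6 × 200 = 60. It also does not apply to emotion regulation and empathy, because all IB-MAI participants receive the relational training, which is half the sample.

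**Module restriction would be costly.** This also stands. The subsets are too small for five classifiers, and an assigned module has no defined meaning in CC, which gets websites by area of distress.

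**Conclusion.** The mismatch is real on the text. With the total sample, no arm variable and a raw-change target, the models predict improvement from any cause. They dilute predictors of response to IB-MAI and cannot distinguish them from prognostic factors, so they do not deliver what hypothesis 4 promises.

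The halving of a pure modifier follows from 1:1 allocation and needs only equal numbers of completers per arm. The 44% control share and the simulated coefficients rest on assumed effects and show the mechanism, not this trial's magnitudes. The document does not support saying that the models are worthless or that the efficacy comparison is compromised: the pooled models are valid prognostic models under the wrong label. The change is worth making before analysis, in proportion to an exploratory aim.

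**What to change.** In section 2.8:

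- Keep the whole sample and the constant 20% hold-out.
- State that both arms are included, and add randomised arm as a feature.
- Add screened problem area (or module), defined from the baseline screening in the same way in both arms.
- Call a variable a predictor of treatment response only if its association with response differs between IB-MAI and CC, shown by an arm-by-feature term or an arm-specific contrast. For LDA and the linear-kernel SVM, product terms must be entered explicitly, because arm alone only shifts the decision boundary.
- Report every other predictor as prognostic for improvement, and word the conclusions on hypothesis 4 to match.
- Do not require models restricted to a single module.

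Arm and screening results are already recorded, so no new data are needed and the training set stays at 160 of 200 completers. The cost is some added analysis and imprecise interaction estimates, since the trial was sized for a main effect of d = 0.40. If the interaction work is judged too imprecise to be useful, relabelling the pooled models as prognostic costs nothing and removes the misleading claim, but it leaves hypothesis 4 unanswered.
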